#### Web-based educational modules

The education implementation strategy will consist of six 10- to 15-min web-based modules, a tip sheet with clinic-specific interpreter access and use information, and four 5-min booster modules, all delivered online, along with quarterly reports on interpreter use to the enrolled provider. Education aims to improve provider motivation and capability related to interpreter use, by increasing conceptual and technical knowledge, enhancing interpreter access skills, shifting beliefs about their own capabilities and the consequences of use or nonuse, and increasing the intention to use an interpreter.

The educational module content is based on Seattle Children’s Hospital’s rigorously developed in-person workshop series, CONNECTing Through Interpreters [49–52]. In partnership with the interactive Medical Training Resources (iMTR) group at the University of Washington (UW; depts.washington.edu/imtr/) and content experts including experienced interpreters and providers, we transformed the workshops into interactive web-based modules. Modules were pilot tested with 15 primary care providers (PCPs) and revised based on feedback. Module-assigned providers will view them at a time and place they choose. We will track when participants access and complete modules as a marker of engagement.

The *online modules* cover 5 topics: (1) importance and fundamentals of good communication (delivered in 2 modules), (2) importance of professional interpreter use and disparities for populations with language barriers, (3) how to use an interpreter effectively, (4) what to do when the interpreted encounter is not going well, and (5) remote interpreter use and system’s challenges. Each module is 10–15 min long with audio, visual, and video content, developed using best practices from adult learning theory. Providers will be prompted to view a new module each week until all have been viewed.

During months 3–6 post-randomization, 4 brief (5 min) *booster modules* will be released, reviewing crucial points from initial modules. Boosters have been found to support behavior change in other settings [87]. Weekly reminders will be sent until they are complete. Providers who complete all modules will be eligible for points for continuing medical education (CME) and/or Maintenance of Certification (MOC); these points must be earned to maintain medical licensure and board certification and thus provide incentive for completion.

The *clinic-specific interpreter access and use information* will be distributed via email. This sheet will include instructions for accessing interpreters in their clinic via the normal process, including the vendor phone number, tips for using the clinic telephones (e.g., how to adjust the speakerphone volume), ideas for streamlining the process, where shared equipment is stored, and how to report problems.

*Feedback to enrolled providers* will be provided quarterly with both strategies, as a report of the percent of visits with patients who use a language other than English for which the provider used professional interpretation.

#### Mobile video interpreting access

The mobile video interpreting access strategy will provide access to mobile video interpreting, technical support, a tip sheet for mobile video interpreting use, and an extra charger, shock-resistant case, disposable antimicrobial sleeves, and a positioning stand to support clinical use of the provider’s own device, along with quarterly reports on the enrolled provider’s interpreter use. Mobile video interpreting-assigned providers can use a study-issued smartphone instead of their own. The mobile video interpreting strategy aims to improve provider motivation, capability, and opportunity related to interpreter use, by decreasing cognitive overload, enhancing interpreter access skills, shifting provider beliefs about capabilities and the consequences of interpreter use, reinforcing use via satisfaction, and altering the environmental context and resources to make access easier and use more rewarding (Table 2).

*Access to mobile video interpreting* is achieved by downloading the application (app) online and then entering an access code linked to a billing account; after being entered, the code is no longer visible. Access can thus be controlled by study staff. Study staff will download and orient providers to the app, demonstrate use, and answer questions. *Technical support* will be offered on demand. A *tip sheet* will be emailed that includes mobile video interpreting instructions and best practices.

Several interpretation vendors have similar apps that can be downloaded onto personal devices but are rarely used in this way. These apps are HIPAA compliant, use end-to-end encryption, and are accessed with one touch (i.e., no additional log in or passwords); no data is downloaded to the device.

*Feedback to enrolled providers* will be provided quarterly with both strategies, as a report of the percent of visits with patients who use a language other than English for which the provider used professional interpretation.

### Study populations and setting

#### Providers

We will enroll 55 PCPs from 3 to 5 primary care organizations in Washington state. These organizations will include both academically affiliated and nonacademic sites and vary in terms of leadership and governance structures. Clinics will enroll based on provider interest, but each provider will choose whether to enroll. Eligible providers will practice at the enrolled clinic at least 40% time and see at least 7 patients requiring interpretation per month, on average. If the provider is proficient in a non-English language, they will see at least 7 patients per month who use a different language (in which they are not proficient). We will enroll and initially randomize 55 providers, to retain 47 through the second interview and 40 through the third (73% retention; see next section for sample size considerations).

#### Patients

We will enroll 3 populations of adult patients or parents of pediatric patients (henceforth “patients”) who use a language other than English, all being seen by enrolled providers. For our *administrative population*, we will include administrative data from all patients who were recorded as using a language other than English in the medical record and were seen by enrolled providers, for the interpreter use outcome. For our *survey population*, we will enroll patients who prefer medical care in the four most common non-English languages across clinics, who are in clinic for an acute concern (e.g., sore throat, new ankle pain). These individuals will be invited to complete a survey (*n* = 648), and a subset will be invited to complete a 20–30 min qualitative interview (*n* = 75). We will also recruit patients for our *video-recording population* (*n* = 100). Patients who use a language other than English with any visit type who consent will be eligible for video recording.

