#### Interpreter use

Interpreter vendor invoices will be collected from companies that clinics currently contract with; mobile video interpreting invoices will be managed by the study team. All professional interpreter invoices (not just mobile video interpreting) will be matched to clinic visits for patients who use a language other than English (all languages) for enrolled providers. We will calculate baseline interpreter use for enrolled providers for the six months pre-randomization and then randomize 1:1 to education or mobile video interpreting, stratified by baseline use and clinic. We will calculate interpreter use, both overall and strategy consistent, continuously throughout phases 1–3; other data collection will end after phase 2.

For analysis, interpreter use will be defined as a dichotomous variable at the level of the clinic visit. Visits with patients who use a language other than English with any billed professional interpreter use will be coded as “yes,” and the remainder will be coded as “no.”

Sample size calculations consider aim 1 group comparisons (mobile video interpreting, education, combination) at the end of phase 2. We assume loss of up to 9 providers (e.g., to job change; 16%) over the study; we expect attrition (up to 27%) in provider interviews and surveys, but that will not impact aim 1 power. With 5796 total encounters with patients who use a language other than English (7 visits/provider/month), we expect 1932 non-English visits per group, which will provide > 80% power to detect a 5% difference in proportion of professionally interpreted visits by groups [46, 57]. This will be readily feasible with administrative data.

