#### Aim 1: Compare the effectiveness of two implementation strategies, alone and in combination, to improve use of interpretation and comprehension for patients/parents with language barriers seen in adult/pediatric primary care settings

We hypothesize that, compared to educational modules, provider access to mobile video interpreting will lead to (*H1*) greater odds of interpreter use for visits with patients/parents with language barriers (primary outcome) and (*H2*) better comprehension among patients/parents with language barriers. We also hypothesize (*H3*) that mobile video interpreting and educational modules together will yield greater odds of interpreter use than either strategy alone.

To test *H1* and *H3*, we will use assigned strategy and data collected during phases 1 and 2. Under the SMART design, comparisons of first-stage interventions, comparisons of second-stage interventions, and comparisons of the adaptive intervention with both stages can be conducted simultaneously using standard software with a technique called a “weighted and replicated” regression approach, using weighted generalized estimating equations (GEE) [66, 97]. Weighted GEE allows us to work with binary outcomes and weights and adjust for clustering within providers. Within-clinic correlations will be assessed by including clinic-specific random effects in our regression models and estimating the intra-cluster correlation coefficients. Significance of the intra-cluster correlation coefficients will be examined by comparing models with and without clinic-specific random effects using likelihood ratio tests. If no strong within-clinic correlation is detected, we will use fixed-effects regression models for their better power; otherwise, estimates and inference based on random-effects regression models will be reported. *H1* and *H3* will be tested using the Wald test and robust standard error estimates [66, 97]. Model-based estimates of odds ratio comparing education to mobile video interpreting or both will be reported, along with 95% confidence intervals [98].

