We will calculate total costs associated with each implementation strategy by summing the above costs. To test *H4a*, we will calculate the ICER for each additional interpreted clinic visit, by calculating the difference in total costs for (i) mobile video interpreting vs education and (ii) mobile video interpreting plus education vs education, and then divide by the difference in number of professionally interpreted visits for providers assigned to (i) mobile video interpreting vs education and (ii) mobile video interpreting plus education vs education. To test *H4b*, we will calculate the ICER for each additional instance of patient comprehension. To do so, we will calculate the difference in total costs for (i) mobile video interpreting vs education and (ii) mobile video interpreting plus education vs education and then divide by the difference in proportion of patients who correctly reported their diagnosis for providers assigned to (i) mobile video interpreting vs education and (ii) mobile video interpreting plus education vs education.

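### H4b sets costs from all visits and languages against a comprehension effect measured only in acute visits in four languages, and H2 is worded more widely than its sample

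*Protocol article*

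**What the plan says.** Under Study populations and setting (Patients), the protocol article defines two populations that matter here. The survey population is "patients who prefer medical care in the four most common non-English languages across clinics" and, among these, those "who are in clinic for an acute concern". The administrative population is wider: "administrative data from all patients who were recorded as using a language other than English in the medical record", with no limit on visit type. The section on interpreter use says that all professional interpreter invoices are to be "matched to clinic visits for patients who use a language other than English (all languages) for enrolled providers".

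Aim 1 states H2 as "better comprehension among patients/parents with language barriers", without limiting visit type or language. The analysis paragraph for H2 then restricts the sample to patients who completed a post-visit survey (n = 648).

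Aim 3 takes its effects from the Aim 1 analyses and bases interpreter costs on actual invoiced use, attributed to the assigned group. H4b takes the same difference in total costs as H4a and is then to "divide by the difference in proportion of patients who correctly reported their diagnosis for providers assigned to" each strategy in the pair. Nothing in Aim 3 limits costs to survey-eligible visits or says that the survey effect is taken to apply to other visits.

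**The concern.** H4b is meant to give a cost per additional instance of patient comprehension. Its numerator covers every visit by a patient recorded as using a language other than English. Its denominator comes only from acute visits in four languages. As written, the ratio is not a cost per gained instance in any single population.

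Correcting the units would not settle this. Turning a difference in proportions into a number of instances needs a count of visits. If all visits are used, the acute, four-language effect is silently carried over to wellness visits, chronic follow-up and rarer languages. If only eligible visits are used, the costs of all the other visits stay in the numerator.

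Aim 3 says the ratios are meant to help leaders of healthcare organizations choose a strategy. Such a reader would take H4b to apply to all of the organization's patients with language barriers, and would read H2 as equally broad.

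**Working it through.** **Inputs from the protocol article**
- 55 providers, up to 9 lost, 7 visits per provider per month, two 9-month phases (Interpreter use; Study design and randomization).
- 648 surveys, 216 per group, 14-point difference in comprehension (Patient/parent comprehension).

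**Inputs that are not given and are assumed**
- *s*, the share of non-English visits that are acute and in the four languages: 0.20 to 0.75.
- *k*, the comprehension effect in ineligible visits as a multiple of that in eligible visits: 0 to 1.5.

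**The plan's own figures.** (55 − 9) × 7 × 18 = 5796 visits; 5796 / 3 = 1932 per group; 648 / 3 = 216 per group. At two-sided 5% (assumed from the 95% confidence intervals) and with no allowance for clustering, 216 per group gives power of at least 0.831 for a 14-point difference over control rates of 30% to 80%. The minimum is near 43% against 57%. The stated figure of at least 80% is reproduced. No sample-size figure depends on the present point.

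**The two halves of H4b**

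| | Visit types | Languages |
|---|---|---|
| Interpreter costs (numerator) | no limit stated | all |
| Comprehension difference (denominator) | acute only | four most common |

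**Choice of visit base.** With a difference of 0.14, the gained instances per group are 0.14 × 216 = 30.2 among surveyed patients, but 0.14 × 1932 = 270.5 among all expected visits. The same cost difference then gives ratios that differ by a factor of 1932 / 216 = 8.9. The choice of population sets the scale of H4b.

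**Case A: the difference *d* is applied to all *N* visits.** The survey-based count of gained instances is *Nd*. The actual count is *N*[*sd* + (1 − *s*)*kd*]. With the same cost on top,

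survey-based ratio / correct all-visit ratio = *s* + (1 − *s*)*k*

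| *s* | *k* = 0 | *k* = 0.5 | *k* = 1 | *k* = 1.5 |
|---|---|---|---|---|
| 0.20 | 0.20 | 0.60 | 1.00 | 1.40 |
| 0.35 | 0.35 | 0.675 | 1.00 | 1.325 |
| 0.50 | 0.50 | 0.75 | 1.00 | 1.25 |
| 0.75 | 0.75 | 0.875 | 1.00 | 1.125 |

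The error vanishes at *k* = 1 for every *s* and changes sign there.

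**Case B: gains are counted in eligible visits only, while costs cover all visits.** Let *F* be the difference in fixed costs and *V* the difference in visit-level interpreter costs over all visits, with the same sign and a similar difference per visit. Relative to a version with matched visit-level costs, the ratio is multiplied by

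(*F* + *V*) / (*F* + *sV*)

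This is 1 if all costs are fixed (*V* = 0) and 1/*s* if none are (*F* = 0): 5 at *s* = 0.20, 2 at *s* = 0.50 and 1.33 at *s* = 0.75.

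The article does not say which case applies.

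**The case against.** A reader might infer that H4b is biased, and in favour of mobile video: acute visits leave little time to arrange the in-person interpreters that providers are said to prefer, so on-demand video may show its largest advantage there. The documents do not support this step. They give no data on comprehension effects by visit type or language. The Background also describes remote interpreting as the only option for uncommon languages, so the four-language limit may leave out visits where remote access matters most. Both groups keep standard interpreter access. The direction is open, and the error may be zero.

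A reader might also infer that H2 is invalid. It is not. The analysis sample is stated openly, and eligibility does not bias the comparison of strategies within it. The article states a hypothesis and draws no conclusion for all patients. What remains is wording wider than the sample.

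The acute restriction itself may be sensible. Comprehension is agreement on the visit diagnosis, and a chronic follow-up or wellness visit may bring no new one. The article does not give this reason, so it is inference, but the restriction is not treated here as a design fault.

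Aim 3 takes the organization's perspective, and an organization that adopts a strategy pays its fixed costs in full, whatever the mix of visits. This stands, and it rules out apportioning fixed costs in the main calculation.

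Finally, an article may leave costing detail to a fuller document. That carries less weight here, because Aim 3 fixes both the numerator and the denominator of H4b, and as fixed they refer to different visits.

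**Conclusion.** The mismatch stands. H4b combines costs from all visits and languages with an effect from acute visits in four languages, and is interpretable for all patients with language barriers only under an equal-effect assumption that is neither stated nor tested.

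No single size can be given. Under the assumed ranges for *s* and *k*, a ratio scaled to all visits lies between 0.20 and 1.40 times the correct one. Counting gains in eligible visits alone against all-visit costs could multiply the ratio by up to 1/*s*. These figures show sensitivity to unknown quantities; they do not estimate an error in the plan.

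For H2 the point is limited to the breadth of the claim. The primary outcome, H1, H3, H4a and the power figures are unaffected.

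**What to change.** - **Matched H4b.** Add a version in which cost and effect refer to the same visits. Restrict visit-level interpreter invoices to acute visits of enrolled providers in the four survey languages, and multiply the comprehension difference by the number of those visits.
- **Fixed costs.** Report modules, set-up and staff time in full, in line with the organization perspective. Show apportionment by visit share only as a sensitivity analysis.
- **All-visit H4b.** If reported, label it as an extrapolation, state the equal-effect assumption, and vary *k* both below and above 1, using the observed *s*.
- **Wording.** State the H2 and H4b conclusions as applying to acute visits in the four survey languages.

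No new data or recruitment is needed. Table 1 already lists visit type from the medical record and administrative data, language is recorded in the medical record, and invoices are already matched to visits. The price is a narrower claim and fewer invoices behind the matched cost estimate. In that version the full fixed-cost difference is also set against fewer visits and weighs more heavily, which is why the apportioned figure should stand beside it.

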### Data collection, study measures, and sample size

Outcome measures include our primary implementation outcome of interpreter use and our secondary effectiveness outcome of patient/parent comprehension. Additional measures related to organizational context, provider-reported barriers and facilitators of interpreter use, and intervention fidelity are laid out in Table 1.

#### Interpreter use

Interpreter vendor invoices will be collected from companies that clinics currently contract with; mobile video interpreting invoices will be managed by the study team. All professional interpreter invoices (not just mobile video interpreting) will be matched to clinic visits for patients who use a language other than English (all languages) for enrolled providers. We will calculate baseline interpreter use for enrolled providers for the six months pre-randomization and then randomize 1:1 to education or mobile video interpreting, stratified by baseline use and clinic. We will calculate interpreter use, both overall and strategy consistent, continuously throughout phases 1–3; other data collection will end after phase 2.

For analysis, interpreter use will be defined as a dichotomous variable at the level of the clinic visit. Visits with patients who use a language other than English with any billed professional interpreter use will be coded as “yes,” and the remainder will be coded as “no.”

Sample size calculations consider aim 1 group comparisons (mobile video interpreting, education, combination) at the end of phase 2. We assume loss of up to 9 providers (e.g., to job change; 16%) over the study; we expect attrition (up to 27%) in provider interviews and surveys, but that will not impact aim 1 power. With 5796 total encounters with patients who use a language other than English (7 visits/provider/month), we expect 1932 non-English visits per group, which will provide > 80% power to detect a 5% difference in proportion of professionally interpreted visits by groups [46, 57]. This will be readily feasible with administrative data.

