### Study design and randomization

This type 3 hybrid implementation-effectiveness study will test two discrete implementation strategies for improving professional interpreter use (primary implementation outcome) and patient comprehension (secondary effectiveness outcome) in primary care. The implementation strategies—interactive web-based educational modules and access to mobile video interpreting—target different sets of barriers to professional interpreter use, an evidence-based practice [20, 21, 34, 82, 83]. Our results will therefore provide insights into how best to promote implementation of a well-studied, well-established practice known to improve outcomes but inconsistently used. As the potency of barriers may vary by provider and clinic, we will test the strategies alone and in combination, using a SMART design, with provider-level randomization.

A total of 55 providers from 3 to 5 primary care clinical organizations will be randomized 1:1 to either education or mobile video interpreting access, stratified by baseline interpreter use and clinic (phase 1; Fig. 2). Randomization will occur within REDCap, using a sequence generated by the study biostatistician and implemented by a research coordinator. After 9 months, providers with interpreter use in the top tertile (within strategy) will remain with the original strategy; those in the bottom two tertiles will be randomized 1:1 again, to continue the original strategy or to add the second strategy to the first (phase 2). After another 9 months of data collection, we will provide free access to both mobile video interpreting and educational modules to all enrolled providers and then track voluntary uptake by those not previously exposed for another 9 months (phase 3). Data collection will include *administrative data* to track interpreter use (primary outcome); *patient surveys and qualitative interviews* to determine diagnosis comprehension (secondary outcome) and communication quality; *provider surveys and qualitative interviews* to assess contextual and intrapersonal barriers and moderators; and *visit video recording* to capture additional barriers and determine fidelity of strategy implementation. We will assess each strategy’s effectiveness, alone and in combination, for improving professional interpreter use and patient comprehension. We will explore mechanisms by which these strategies work and evaluate the relative strategy-specific costs.

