#### Patient/parent comprehension

Patient comprehension will be determined by asking surveyed patients (*n* = 648) to report the diagnosis they received during their visit with an enrolled provider. The parent-reported diagnosis will then be compared to the provider-documented diagnosis, which trained abstractors will have abstracted from the EMR. Two coders blinded to study assignment will compare the documented diagnosis to the patient-reported diagnosis to determine comprehension, coded as yes, concordant; no, not concordant; or unclear, based on the standard of whether a different follow-up provider would likely know the diagnosis based on the information provided by the patient. For analysis, comprehension will be coded as yes or no/unclear. We have successfully used these procedures previously [46].

In addition to measuring comprehension, the survey will use validated measures to collect demographics and satisfaction with communication and interpretation. The tablet-based survey will have an audio feature to allow patients to read or hear the questions in 4 non-English languages. The survey will be completed in the clinic whenever possible; otherwise, the patient will complete it within 7 days, independently online or over the telephone with a bilingual research coordinator or professional interpreter.

Based on aim 1 analyses, with 216 completed patient surveys per group (648 total), we will have ≥ *80% power to detect a 14% difference in diagnosis comprehension by group* [46]. This will also be feasible, achieved by surveying 7–12 patients per clinic per month for 18 months.

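### The stated 1932 visits per group is an 18-month total split in three, but the SMART yields only 966 visits on the combination, so the power claim is not assured for H3

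*Protocol article*

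**What the plan says.** The Study design and randomization section describes two stages. First, "A total of 55 providers from 3 to 5 primary care clinical organizations will be randomized 1:1 to either education or mobile video interpreting access". After 9 months, the top tertile within each strategy stays as assigned, and "those in the bottom two tertiles will be randomized 1:1 again, to continue the original strategy or to add the second strategy". Phase 2 lasts another 9 months. Phase 3 then opens both strategies to everyone.

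The Interpreter use section sets the sample size: "Sample size calculations consider aim 1 group comparisons (mobile video interpreting, education, combination) at the end of phase 2". It allows for attrition: "We assume loss of up to 9 providers (e.g., to job change; 16%) over the study". It then gives the counts, "With 5796 total encounters with patients who use a language other than English (7 visits/provider/month), we expect 1932 non-English visits per group", and claims more than 80% power for a 5-point difference between groups.

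The Patient/parent comprehension section divides 648 surveys into 216 per group for at least 80% power at a 14-point difference. The surveys come from 7 to 12 "patients per clinic per month for 18 months".

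Under Aim 1 of the Data analysis section, H1 and H3 use data from phases 1 and 2. H3 holds that the two strategies together produce more interpreter use than either one alone.

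**The concern.** The per-group figure treats mobile video, education and combination as three groups of equal size, each observed for the full 18 months. The design does not produce that. The combination first exists at the second randomization, so it can accrue visits only in phase 2, and only from providers who were re-randomized and drew the added strategy.

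H3 depends on this group. If its expected size is half of what is stated, the power claim does not carry over to H3. A null result for the combination could then be read as adequately powered evidence that adding the second strategy brings nothing.

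**Working it through.** **Inputs.** 55 providers and 1:1 first randomization (Study design and randomization); loss of up to 9 and 7 visits per provider per month (Interpreter use); two phases of 9 months; top third stays, bottom two thirds re-randomized 1:1 (Study design and randomization); 648 surveys over 18 months (Patient/parent comprehension). The article gives no base rate and no alpha for the power claim. I assume two-sided 0.05 and vary the base rate.

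**The plan's own figures.**
- Providers retained: 55 - 9 = 46.
- Visits over 18 months: 46 x 7 x 18 = 5796, as stated.
- Per group: 5796 / 3 = 1932, as stated.
- Surveys per group: 648 / 3 = 216, as stated.

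Other bases do not reproduce the total: 55 providers give 55 x 7 x 18 = 6930, and 27 months give 46 x 7 x 27 = 8694.

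**Visits under the SMART.**
- Phase 1, each first-stage arm: 23 x 7 x 9 = 1449. Combination: 0.
- Providers on the combination in phase 2: 46 x 2/3 x 1/2 = 15.33.
- Combination visits in phase 2: 15.33 x 7 x 9 = 966.
- Providers on each single strategy in phase 2: 23 x 2/3 = 15.33 (one third stays as responders, one third is re-randomized to continue), again 966 visits.
- 18-month totals: 1449 + 966 = 2415 for each single strategy and 966 for the combination. Check: 2415 + 2415 + 966 = 5796.

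**Power for a 5-point difference.** Power = Φ(d / SE - 1.96), with SE = √[p1(1-p1)/n1 + p2(1-p2)/n2] and independent visits. Example for 966 vs 966 at 50% vs 55%: SE = √[(0.25 + 0.2475)/966] = 0.0227; 0.05/0.0227 = 2.20; Φ(0.24) ≈ 60%.

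| Rates | 1932 vs 1932 (stated) | 966 vs 966 | 966 vs 2415 |
|---|---|---|---|
| 50% vs 55% | 88% | 60% | 75% |
| 70% vs 75% | 94% | 69% | 85% |
| 80% vs 85% | 98% | 83% | 94% |

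The last column is only a guide. The single-strategy totals include phase 1 visits from providers who later receive the combination, so the two samples are not independent. Clustering of visits within providers is ignored throughout and would generally lower these figures.

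**Surveys, if spread evenly over months and providers.**
- Pace: 648 / 18 = 36 a month; phase 2: 36 x 9 = 324.
- Combination: 324 / 3 = 108.
- Each single strategy: 324 / 2 + 108 = 162 + 108 = 270. Check: 270 + 270 + 108 = 648.
- Power at 50% vs 64%, same formula: 84% at 216 vs 216 (stated), 56% at 108 vs 108, 72% at 108 vs 270.

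**The case against.** The best defence is that 1932 follows from a particular definition of a group. At the end of phase 2 the three groups hold 46 / 3 = 15.33 providers each, and 15.33 x 7 x 18 = 1932 if each provider's whole 18 months is credited to the final group. This explains the figure but does not rescue it: half of the visits then counted as combination took place before re-randomization, on one strategy only.

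A second defence points to the weighted and replicated analysis, in which each embedded adaptive strategy also has 15.33 x 126 = 1932 visits once responders are replicated. But there are four such strategies and they overlap. The sample-size text names three groups whose sizes add up to 5796.

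Other objections do stand, and they limit the point.
- **Base rate.** None is given, and rates near 50% are close to the worst case. The table shows the 80% level being met at some higher rates.
- **Visit rate.** Seven visits a month is also the eligibility minimum, and the loss is up to 9 providers. With no loss the combination would have 55/3 x 63 = 1155 visits. At 12 visits a month it would have 15.33 x 12 x 9 = 1656. Reaching 1932 would take 14 a month. So 966 is the plan's own expectation, not a ceiling.
- **Surveys.** The article does not allocate surveys to phases or groups, so 108 depends on even accrual. H2 compares mobile video with education, and H3 concerns interpreter use. No hypothesis tests comprehension under the combination; only an odds ratio for both strategies is to be reported.
- **Separate contrasts.** Splitting the re-randomized providers by first-stage arm gives still smaller samples, but the article plans one weighted model and not that comparison.

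**Conclusion.** The per-group count is wrong as written. At the plan's own 7 visits a month and 46 providers, the combination has 966 visits, half of 1932, while each single strategy has 2415. That part rests only on the article's figures.

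The effect on power is conditional. For a 5-point difference in contrasts with the combination, power ranges from about 60% (50% vs 55%) to 83% (80% vs 85%) at 966 vs 966, and from about 75% to 94% at 966 vs 2415. This assumes independent visits and two-sided alpha 0.05. The claim of more than 80% is therefore not assured for H3.

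A reader might infer that H3 is certain to be underpowered, that the combination group cannot reach 1932, or that the trial's main comparison is compromised. The article does not support these readings: the base rate is not stated, actual visit volume may exceed the minimum, and over phases 1 and 2 the two strategies compared in H1 have more visits than claimed.

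The survey shortfall (about 108 instead of 216, with 56% to 72% power at 50% vs 64%) holds only under even accrual. It affects the reported odds ratio for both strategies, not H2.

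**What to change.** 1. In the Interpreter use section, replace the single per-group figure by expected visits by phase and strategy: phase 1, 1449 per arm; phase 2, 966 each for mobile video, education and combination; 18-month totals 2415 / 2415 / 966.
2. State power separately for H1 and for the combination contrasts under H3, over a range of base rates, and name the data (phase 2 only, or both phases) on which each statement rests.
3. In the Patient/parent comprehension section, either give the survey counts as conditional on even accrual (about 270 / 270 / 108) or collect more of the fixed 648 surveys in phase 2.

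This is a rewording of the sample-size text. It needs no extra providers, visits or surveys. The cost is a less favourable stated power for the combination contrasts.
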